## Abstract

**Background:**

Mindfulness training (MT) for parents of adolescents has been shown to improve mental health and stress-related outcomes in individuals and their families. Studies of MT among young people are mainly delivered in educational or clinical settings, and there is a need for controlled studies on both parent-directed and adolescent-directed approaches. It is unclear whether MT has preventive effects for substance use outcomes. The primary objective of this trial is to evaluate the effectiveness of family-based MT targeting both adolescents and their parents to prevent adolescent substance use and enhance neurobehavioral self-regulation skills that play a major role in addiction development and mental health.

**Methods/design:**

The trial design is a superiority, two-arm, randomized controlled trial in which families will participate either in the full curriculum of the evidence-based Strengthening Families Program 10–14 (SFP 10–14, German adaptation) or in a mindfulness-enhanced version of this program (SFP-Mind). Both seven-session interventions are highly structured and will each be delivered over a period of approximately 7 weeks. The experimental intervention SFP-Mind is a modified version of the SFP 10–14 in which some elements were eliminated or changed to enable the inclusion of additional parent-directed and adolescent-directed mindfulness components. The primary outcome is adolescent self-reported alcohol use based on an alcohol initiation index at 18-month follow-up. Dispositional mindfulness, impulsivity, and emotion regulation will be included as secondary outcomes and potential mechanisms of action. The study will recruit and randomize 216 adolescents, aged 10–14 years, and their parents who will be followed up for 18 months.

**Discussion:**

This trial aims to evaluate the effectiveness of SFP-Mind for family-based prevention of substance use and promoting mental health in adolescence.

**Trial registration:**

German Register of Clinical Studies, DRKS00015678. Registered on 25 February 2019.

## Background

Substance use disorders (SUDs) are among the most frequent and costly mental disorders, both in the general population and among youth [1]. More than 15% of disability-adjusted life years (DALYs) worldwide are attributed to adolescents and emerging adults, with increased risks associated with all types of abusive substances [2]. Compared to the general population, the prevalence for SUDs is higher among young people in western cultures where excessive drinking and other substance abuse usually peaks in emerging adulthood [3, 4]. In Germany, as in most industrialized countries, alcohol is the primary substance abused by teenagers. Although youth drinking in Germany and Europe is moderately decreasing [5, 6], excessive drinking remains high compared to other regions in the world, such as the USA [7], and a substantial proportion of school-aged youths drink alcohol at levels associated with serious risk of harm [8]. Binge drinking directly leads to the placement of more than 23,000 German adolescents per year in emergency care (EC) for acute alcohol intoxication, with indirect substance-related EC cases far exceeding this number [9]. Other short-term and long-term consequences associated with the abuse of alcohol and other substances include serious injuries, violence, fatal road accidents, high-risk sexual activities, school drop-out, development of mental and addictive disorders, heart disease, and cancer as well as impairments of neurocognitive function and brain development [8].

Adolescence may be particularly important for preventive interventions because this period is accompanied by a rapid development of neurocognitive systems that promote novelty-seeking and sensation-seeking alongside risk-taking, with a growing interest in new exciting experiences, including the experimentation with substance use [10]. SUDs (and substance use) are typically initiated in adolescence [11]. Moreover, adolescence constitutes the final maturation phase before adulthood stability [12], and is characterized by heightened susceptibility to peer influences toward risk-taking behavior in this developmental stage [13]. Reducing the risk of SUDs and associated problems through effective interventions during the key developmental window of adolescence is a major public health priority [14].

Previous findings have demonstrated the importance of the family system as an early proximal context for youth development, and the family’s role in early-onset and accelerated problem substance use and related mental health problems. This research provides a strong rationale for prevention based on family-associated risk and resilience factors [15–17]. For example, parents influence their offspring’s substance use by their own substance use, by setting alcohol-related rules and norms, and by monitoring children’s whereabouts [18]. Moreover, parents contribute substantially to the development of self-regulation, psychological functioning, and adaptive strategies for managing negative emotions [19, 20]. Developmentally, the acquisition of self-regulatory competencies emerges from childhood onward; that is, during a time period in which parental influence is high and the social salience of peers is lower than in adolescence [21]. Supportive family relationships have proven themselves to be protective factors against the development of SUDs [22]. Parents with good socioemotional skills can effectively buffer vulnerability for mental disorders among their children, thus contributing to the development of resilience [23]. Programs aimed at promoting social–emotional skills in young adolescents are considered more effective when a carer is involved [15, 24]. Similarly, substance use prevention programs among children and adolescents, which are primarily school-based [14, 25], can be more effective when they also address family-based risk and resilience factors [15, 26].

The Strengthening Families Program for Parents and Youth 10–14 (SFP 10–14) [27] has established an evidence base for preventing the onset and escalation of adolescent substance use and other problem behavior [16, 17, 28–30]. Although several replication trials in European countries have not yielded the same desirable effects [31, 32], the SFP 10–14 is currently one of the most widely disseminated evidence-based prevention programs to promote individual (intrapersonal and interpersonal) competencies and familial resources for healthy and active development, and socioemotional resilience [33]. In our own randomized controlled trial (RCT), we found that the SFP 10–14 is feasible and effective in preventing tobacco use and conduct problems, especially in families with children who have an elevated psychosocial risk load [34, 35]. However, our study results, as well as the other replication trials [31, 32], suggest that program effects could be improved.

An emerging literature base suggests that mindfulness training (MT) may be a helpful addition to such programs as a strategy to target neurocognitive factors [36–40]. Mindfulness is commonly conceptualized within a framework of self-regulation and involves full attention to present-moment experience with an attitude of acceptance, non-judgment, and openness [41]. Clinical and neuroscientific research [36, 38, 42–49] indicates that mindfulness skills can be acquired by training, and that they are associated with improved cognitive flexibility and affective stability, including (inhibitory) control of attention, emotion regulation, and stress reactivity. Taken together, this research supports the notion that MT can foster improvements in top-down control and help individuals manage cognitions, feelings, and behaviors more effectively. These factors not only play a major role in repetitive addictive behaviors [12, 36–38, 40, 48, 50–52], but they also predict the initiation and onset of substance abuse problems and related risks [53, 54], as well as a range of other externalizing and internalizing psychiatric difficulties, which often precede SUD development [55–58].

The evidence base for versions of MT-based interventions is more established for adult than for adolescent populations. However, based on the positive results of a broad range of psychological and clinical outcomes (e.g., [48]), there is growing interest in the application of MT in youth populations in clinical and non-clinical settings [42, 43, 45, 46]. Although most of this research is thus far preliminary (more rigorous clinical trials are underway [59–61], existing studies overall indicate applicability, safety, and initial efficacy of developmentally appropriate versions of MT for children and adolescents. This generally supports the idea that MT can have a significant impact on health and resilience among children and adolescents.

Most existing MT-based prevention approaches were implemented in educational settings [42, 43] while rigorous prevention studies in other non-clinical settings, such as the family, are still lacking. However, initial results (two trials are currently underway [59, 60]) indicate that teaching parents to apply mindful practice in everyday interactions with their children (*mindful parenting*) can positively influence stress-sensitive cognitive and emotional processes relevant for emotional well-being within families, and healthy child development in families in general [62] as well as in families with adolescents exhibiting externalizing behaviors [63]. Coatsworth et al. [64, 65] integrated elements of mindful parenting into the SFP 10–14 (Mindfulness-enhanced Strengthening Families Program, MSFP). Their randomized controlled trial showed that teaching parents mindfulness in combination with parenting skills was superior to the standard SFP 10–14 in several domains of family functioning, in youth behavior management, and in parent well-being (effect sizes after 12 months: *d* = 0.19–0.46). The study indicates that integration of MT for parents into the SFP 10–14 is feasible and associated with enhanced program effects in family and parenting outcomes. However, the study does not include data on substance use and other child-level problem behavior-related outcomes; furthermore, MT was only delivered to the parents.

Since the development of self-regulation and other socioemotional competencies largely happens during the preadolescent period, a phase in which parental influence is still comparably strong, the delivery of MT to modulate risk factors of SUDs and associated psychopathology seems conceptually plausible. Given this and the promising initial results of child and adolescent-related MT approaches, we aim to integrate both child-directed MT and mindful parenting components into the proven structure of the SFP 10–14. We will encourage parents to support their adolescents in practicing mindfulness. We shall test the effectiveness of this mindfulness-augmented program in preventing adolescent alcohol use and improving self-regulation at 18-month follow-up as well as its impact on a spectrum of further individual and family-level outcomes such as parenting skills, child behavior, and family cohesion. We expect and hypothesize that adding mindfulness to the SFP 10–14 will increase the programs’ effectiveness on these outcomes.

## Methods/design

### Study design

We will apply a superiority, two-arm randomized, prospective, observer-blind controlled trial in which an MT-enhanced family-based prevention program will be compared with the SFP 10–14, a previously established efficacious “standard” program version without MT components. This program has been shown to improve symptoms of psychopathology and to delay uptake of substance use in previous studies [28–30], including a German adaptation trial [34]. Intervention conditions in both trial arms are comparable in the frequency and duration of personal contacts. Although inclusion of an additional no-treatment control group in a three-arm trial appeared a desirable option, we consider a two-arm trial adequate for two reasons: firstly, it is an adequate design to address the primary research question, whether MT adds value over the evidence-based standard program version (for a similar approach, see [59, 60, 65]); and, secondly, recruitment is often limited because program deliverers in the field are reluctant to refer families to RCT studies with non-active or minimal control group designs [66, 67].

### Participants and eligibility

Study participants will be children and adolescents aged 10–14 years and their parents or primary caregiver (one adolescent and one carer per family will be included in the analysis; the oldest adolescent aged between 10 and 14 years and the carer who attends the most sessions will be defined as index participants; in the case of equal participation of carers, inclusion will be decided by chance). We aim to recruit 216 families. Families will be excluded if the adolescent exhibits clinical symptoms of psychosis and/or suicidality and/or if family members’ limited knowledge of the German language compromises survey and group participation. The participation of the child or adolescent must be confirmed with written consent from all of their legal guardian(s) alongside that of the child or adolescent. The carer must confirm their own participation via written consent.

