### Setting and recruitment

Recruitment shall take place at community-based child and family service institutions in the region of Hamburg, Germany, which will be chosen as recruiting centers if they reach a sufficient amount of families with their own qualified preventive service programs. As the SFP 10–14 is not routinely implemented in Hamburg, we will set up the required infrastructure for recruitment and program implementation in cooperation with and with support from the local authorities, as we have done for a similar study in the past [34]. Multiple recruitment strategies will be employed to reach a sufficient number of recruitment centers; recruitment includes distribution of written information and presentation of the program goals and study procedures by project representatives via local professional networks and specified agencies in the family health care and social service sector. Additionally, we will start initiatives to raise awareness in educational settings and at authority-level meetings.

Potential referrers will be informed about all aspects of the study and will agree to deliver both program versions in accordance with the study procedures, particularly those that concern randomization procedures, ethical standards, and qualified intervention delivery. Referring institutions will recruit potential participants and inform them about the prevention programs and the study procedures. Consent to participate in the family program (experimental or control) will take place prior to the baseline assessment. Interested families will be visited by a member of the research team for subsequent eligibility assessment and enrolment into the study. Written informed consent, with emphasis on withdrawal rights and ethical aspects as well as all relevant conditions of trial participation, will be obtained during the family visit. Baseline data will be collected before randomization. Trial participants are subsequently randomized to one of the two trial conditions. Recruitment/trial inclusion will be ongoing over a period of approximately 12 months. Figure 1 displays the anticipated CONSORT participant flow.

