### Baseline assessments and follow-ups

Study outcomes for adolescents and their parents/carers will be assessed by trained research staff blinded to the intervention condition at the families’ homes. Participants will be surveyed at baseline (prior to randomization), post intervention (approximately 8 weeks after baseline), as well as 6 months and 18 months (follow-ups) after post assessment. Fidelity and adherence data (i.e., ratings of training sessions) will be gathered during the intervention period (7 weeks). Figure 2 shows an overview of measures from study participants at each time point.

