### Analysis plan

Analyses are planned and supervised by the trial statistician (AD). Study eligibility and enrollment will be summarized according to the CONSORT statement [106]. Descriptive statistics of baseline variables will be assessed by intervention arm. Analyses will be based on the intention-to-treat population, thus including data from all participants who provide baseline data and are subsequently randomized to one of the two trial conditions. Missing follow-up data will be imputed using multiple imputation methods. For the primary analysis, a mixed, linear, repeated-measurement ANCOVA will be conducted, with alcohol initiation (in the form of an initiation index) as the dependent variable; group, time, and interaction between group and time and recruitment center as fixed effects; baseline scores of alcohol use as covariates; adolescent and intervention groups within the study arm as random effects; and time as a repeated effect. The contrast between both groups at the 18-month follow-up will be assessed in a confirmatory manner. We will report adjusted group differences with corresponding 95% confidence intervals (CIs), *p* values, and Cohen’s *d* effect sizes. A systematic examination of factors associated with loss to follow-up will be conducted. The two-sided type I error will be set at 5%. An additional analysis will be conducted on a per-protocol data set as sensitivity analysis. A further sensitivity analysis will be carried out using the data set with all available cases (without any imputation of missing data). The secondary outcomes as well as a potential moderating role of individual and family-level variables and adherence to the intervention and engagement in home practice will be examined in an exploratory manner with appropriate methods. The other model parameters will be set as in the primary outcome analysis. The safety endpoints will be determined using frequency tables and, if possible, using mixed logistic regressions to compare the event frequencies. Interim analyses are not planned. A detailed statistical analyses plan will be prepared and finalized before the code is broken. Statistical analyses will be carried out with SPSS Version 23 or newer (IBM Corp., Armonk, NY, USA).

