### Methods against bias

We take the following action to minimize potentials for biased results. Assessments will be conducted by trained interviewers unaware of the study condition, at home and individually in separate rooms for participating family members to ensure privacy and confidentiality and to reduce drop-out. Blinding of families and intervention facilitators is not possible. To maintain program retention, during the family sessions we offer child care for families who have younger siblings they cannot leave at home alone [69]. Moreover, participating families will be financially rewarded for complete program retention and for each completed follow-up data collection. To avoid crossover in the intervention groups, we aim for implementation of parallel group training with regard to both intervention conditions.

Data management will be performed locally following the guidelines of Good Clinical Practice (GCP) and will be monitored (including source data verification), collected, and preprocessed by the Clinical Trial Center North, thus an external clinical research organization (CRO).

A Data and Safety Monitoring Board (DSMB) will be implemented once the recruitment has started with regular meetings (preferably by telephone conferences), with an open and closed part with and without the coordinating investigator. The DSMB will monitor study and recruitment progress, protocol deviations, loss-to-follow-up data, serious adverse events (SAE) and adverse events (AE), and all problems of the study and decide independently from the coordinating investigator whether the study can be continued or a recommendation is given to change the design or stop the trial. The members of the DSMB will be experienced scientists who are not otherwise involved in the study, independent of the investigators and the trial sponsor, and will have no conflict of interests.

Recruitment centers and all researchers conducting the consenting process and baseline assessments will be repetitively trained to conceal any information which could lead the participants to associate an intervention timing with an intervention arm in order to improve allocation concealment.

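### The analysed carer is picked by session attendance after randomisation, so the arms' parent-completed secondary outcomes are not protected by randomisation in families with more than one participating carer

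*Protocol article*

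**What the plan says.** Under Participants and eligibility, "one adolescent and one carer per family will be included in the analysis". The index adolescent is "the oldest adolescent aged between 10 and 14 years", which is settled by age. For the adult, "the carer who attends the most sessions will be defined as index participants"; and "in the case of equal participation of carers, inclusion will be decided by chance". The tie rule shows that more than one carer per family is expected to take part, at least in some families.

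The order of events is fixed elsewhere. Setting and recruitment says "Baseline data will be collected before randomization", and the seven sessions follow randomisation. Methods against bias says "Blinding of families and intervention facilitators is not possible". The Analysis plan says "Analyses will be based on the intention-to-treat population" and defines that population as participants with baseline data who are then randomised. It treats secondary outcomes as exploratory.

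The article does not name an index carer at baseline, and it plans no sensitivity analysis for this choice.

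**The concern.** Whose questionnaires enter the parent-completed outcomes is decided by behaviour after allocation, and three features of the design could make that behaviour differ by arm:

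- **Knowledge of the programme.** Carers know which programme they are in when they decide who goes.
- **Content.** SFP-Mind adds mindfulness modules for parents and asks them to support the adolescent's home practice (SFP-Mind section).
- **Timing.** The randomisation section allows for carers' weekday absences and moves a family whose constraint does not fit the allocated slot. Methods against bias trains staff not to let participants link a time slot with an arm. Both imply that the arms may meet at different times. Where each of two carers is free at only one of those times, allocation alone can settle who attends.

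If the arms draw different kinds of carer, a difference in parental stress, mindfulness or family functioning could partly reflect who was measured. The introduction hypothesises gains in parenting skills and family cohesion, so these outcomes will be read with interest.

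**Working it through.** **1. The plan's own figure.** The only stated size calculation is for the primary outcome: d = 0.40, r = 0.30, 80% power, two-sided 5%, 91 per arm. With residual SD √(1 − 0.30²) = 0.954, the noncentral-t ANCOVA gives 80.3% power at 91 per arm and 79.9% at 90, so 91 is reproduced. Allowing for 15% loss, 91/0.85 = 107.1, rounded up to 108 per arm, or 216 in total. None of this depends on the carer rule.

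**2. Order of events.** Baseline, then randomisation, then sessions, then the attendance count, then the index carer. The adolescent's place in the analysis depends on age alone; the carer's depends on a variable measured after allocation.

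**3. Simple illustration of size.** The document gives none of these inputs; all three are assumptions.

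- Share of families with two participating carers: 50% to 70%
- Arm difference in which carer attends most: 20 percentage points
- Mean difference between the two carers on a scale: 0.3 to 0.5 SD

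Bias = share × arm difference × carer difference.

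- Low: 0.5 × 0.2 × 0.3 = 0.03 SD
- High: 0.7 × 0.2 × 0.5 = 0.07 SD

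With 91 per arm, the standard error of the adjusted difference is 0.954 × √(2/91) = 0.141 SD. The bias is then 0.03/0.141 = 0.2 to 0.07/0.141 = 0.5 standard errors, and a nominal 5% error rate becomes roughly 5.5% to 8%. If the difference between carers is stable over time and the analysed carer's own baseline is used, adjustment leaves a fraction 1 − r = 0.7, or 0.02 to 0.05 SD.

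**4. A second model, also on assumed inputs.** Here there is no treatment effect, the two carers in a family are independent, r = 0.30, and attendance correlates with the carer's follow-up score at ρ₀ in one arm and ρ₁ in the other. The adjusted bias is approximately share × (1/√π) × (ρ₁ − ρ₀) × (1 − r²), with 1/√π = 0.564. For example, 0.5 × 0.564 × 0.3 × 0.91 = 0.077. Simulation (400,000 families per arm) gives the following adjusted bias in SD, with the error rate at 91 per arm in brackets:

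| ρ₀, ρ₁ | 25% two-carer | 50% two-carer | 100% two-carer |
|---|---|---|---|
| 0.3, 0.3 | 0.001 (5.0%) | 0.001 (5.0%) | 0.001 (5.0%) |
| 0.2, 0.4 | 0.024 (5.3%) | 0.057 (6.9%) | 0.110 (12.2%) |
| 0, 0.3 | 0.040 (5.9%) | 0.077 (8.5%) | 0.157 (19.9%) |
| 0, 0.5 | 0.065 (7.4%) | 0.131 (15.2%) | 0.255 (43.7%) |

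In this model baseline adjustment removes only about 10% of the bias. The first row is the important one: selecting the better-attending carer does no harm to the comparison when it works alike in both arms.

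**5. Scale for comparison.** The introduction cites d = 0.19 to 0.46 for parent and family outcomes in the nearest earlier trial. The illustration in step 3 is 0.03/0.19 = 16% to 0.07/0.19 = 37% of the lower end.

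**The case against.** The strongest reply is that the reach is narrow and differential selection is not shown. The primary outcome is reported by the adolescent, the parent outcomes are exploratory, and single-carer families cannot be affected. The article says that contact frequency and duration are comparable between arms. It describes child care and retention rewards without distinction by arm, and it aims to run the groups in parallel. Home practice takes place outside the sessions and does not count as attendance. All of this stands and limits the point. It does not remove it, because parent content and possibly timing still differ and families know their arm.

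A reader might infer several stronger things that the document does not support:

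- **That the rule contradicts the stated intention-to-treat analysis.** Families are the randomised unit, and the rule drops none and moves none between arms. The departure is at carer level, in who represents a retained family.
- **That leaving ties, or families in which nobody attends, to chance is a flaw.** A random draw is unrelated to arm.
- **That the analysed carer may lack a baseline value.** This is only a possibility. The analysis population is limited to participants with baseline data, and the available text does not say which carers are surveyed at baseline (Figure 2 is not shown).
- **That choosing the most engaged carer is biased in itself.** Under equal selection the bias is about zero.

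There is also a fair argument for the present rule: it measures the adult who received most of the programme. That is a legitimate supportive question, but it is not the randomised comparison.

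**Conclusion.** The point holds in a limited form. For parent-completed secondary outcomes, in families with more than one participating carer, the analysed person is chosen by a variable that allocation can influence. Randomisation does not protect that comparison, and nothing in the article corrects it. The primary outcome, the sample size and the confirmatory type I error are untouched.

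The size cannot be derived from the document, because it gives neither the share of two-carer families nor any data on attendance by carer. On the assumed inputs above, the bias is about 0.03 to 0.07 SD before baseline adjustment. Values above 0.1 SD appear only in the second model, under strongly differential selection with half or more of families having two carers, or with two carers in every family. With equal selection it is about 0. The case for change rests on the definition being avoidable and cheap to correct, not on a demonstrated large bias.

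**What to change.** Name the index carer at the baseline visit, before randomisation: the primary caregiver, or a random draw if the role is shared. Analyse that carer regardless of attendance. For families already enrolled (recruitment began in December 2019), choose among carers with baseline data by a rule that ignores attendance. Keep the most-attending carer as a supportive analysis, and report by arm how often the two definitions pick different people.

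The cost is a line in the enrolment procedure and a line in the statistical analysis plan, which the article says will be finalised before the code is broken. The sample size does not change. The real downside is that in some families the analysed carer will have attended fewer sessions, which may dilute the estimated effect on parent outcomes; the supportive analysis shows how much the choice matters.
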